**Fig 1 pone.0289508.g001:**
[figure not shown]
Timeline for study design and investigative measurements. (Top) Timeline of prospective longitudinal study. Visit 1 and Visit 2 (red) includes: Physiological and cognitive assessments and blood draw. (Bottom) Investigative measures including physiological and cognitive assessments and circulating factors recorded at Visit 1 and 2 (red) and baseline MRI recorded at diagnosis of MCI prior to COVID-19 pandemic, and 18-month follow-up MRI (black). Red arrows indicate deep WMH, and orange arrows indicate periventricular WMH. Abbreviations: White matter hyperintensity (WMH), Functional near-infrared spectroscopy (f-NIRS), Electroencephalography (EEG), Dynamic retinal vessel analysis (DVA), Laser speckle contrast imaging (LSCI), Flow mediated dilation (FMD).

### 2.3 Study setting

This is an ongoing study in the Translational Geroscience Laboratory in the Department of Neurosurgery at the OUHSC in full collaboration with the OUHSC Department of Neurology and Oklahoma City VA Medical Center. The University of Oklahoma Medical Center serves the state of Oklahoma and all surrounding states, and the VA Medical Center serves up to 63,000 veterans in Oklahoma and multiple counties in Texas. Hence, patients will be evaluated for eligibility, and based on patient flow through the Department of Neurology and VA, up to 200 patients will be enrolled through our clinical collaborators in the Department of Neurology.

### 2.4 Sample size estimation

For longitudinal study design, assessing COVID-19’s effect on progression to dementia over the course of 18-months in patients with MCI, our sample size estimation is based on data from *n =* 118 patients diagnosed with MCI prior to COVID-19 pandemic. These data showed a significantly increased progression rate to dementia in MCI patients who contracted COVID-19 (10/18 patients; 55.6%) compared to patients who were never infected (23/100 patients; 23%) (*p =* 0.011) [21]. Due to continued monitoring of patients through semiannual neurologic visits as standard-of-care, we expect that dropout will not exceed the rate of 10%. Based on seroprevalence reports and total number of confirmed cases in the aging community, we anticipate that 5–15% of the control group will develop COVID-19 through the 18-month protocol. Additionally, based on the CDC 2021 national mortality data for persons aged 65 and older, accounting for COVID-19 related death, we will enroll additional participants to account for the 2–5% death per 100,000 population. Therefore, to control for these adverse events, we will require up to 200 MCI patients with and without a history of COVID-19.

### 2.5 Inclusion criteria

Ages between 55 and 85 years oldDiagnosis of MCIAvailability of an MRI scan before study enrollmentPatients with a history of COVID-19 were confirmed by PCR or serology.

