## 2. Study aims and protocol

### 2.1 Study aims

To determine whether history of COVID-19 infection in patients with MCI disrupts systemic endothelial function and impairs NVC response compared to MCI patients with no history of COVID-19 infection.To determine whether history of COVID-19 infection aggravates the impairment of fluid cognitive abilities in patients with MCI.To determine whether impairment of NVC responses in recovered COVID-19 patients with MCI contributes to increased conversion of MCI to dementia.To determine whether COVID-19 related increases in white matter hyperintensity (WMH) burden contribute to conversion of MCI to dementia.

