### 2.2 Study design

This study will test the hypothesis that COVID-19 infection promotes systemic endothelial dysfunction, impairing NVC responses and promoting white matter damage, contributing to the progression of MCI to dementia. To test this hypothesis, we will prospectively follow patients, who are diagnosed with MCI, with or without history of SARS-CoV-2 infection, for 18 months. The timeline for study design and investigative measurements are represented in **Fig 1.** Study participants will be evaluated for eligibility and enrolled through neurology clinics at the University of Oklahoma Health Sciences Center (OUHSC) and Oklahoma City Veterans Affairs (VA) Medical Center (Visit 0). Upon enrollment, patient history, demographic data, standard risk factors for dementia, cognitive status and WMH status (MRI scan) will be recorded. Blood collection, cognitive tests (NIH-toolbox, *n-*back), and baseline physiologic assessments for peripheral endothelial function (flow-mediated dilation [FMD], laser speckle contrast imaging [LSCI]) and NVC responses (functional near-infrared spectroscopy [fNIRS], dynamic retinal vessel analysis [DVA]) will be conducted at the OUHSC Translational Geroscience Laboratory (Visit 1). Study participants will undergo semi-annual clinical neurologic evaluations as a part of standard care. In addition to COVID-19 status since enrollment (e.g., PCR+/-, symptoms), progression from MCI to dementia will be assessed by the clinical neurology team with final adjudication made through consensus management conferences. Repeat of all physiological assessments, cognitive tests, and serum collection will be performed at month 18 (Visit 2), and the second MRI scan will be performed. If some participants decide to terminate their participation in the study for any reason, they will be invited to an early termination visit, which will include the same evaluations as in Visit 2.

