**Comorbidities**	Demographic	Past medical history and/or ongoing medically controlled for conditions	Nominal
**SARS-CoV-2 Variant**	Demographic	Estimated variant based on time (month and year) patient was infected with SARS-CoV-2	Nominal
**Vaccination History**	Demographic	Number of doses, vaccine manufacturer	Nominal
**Education**	Demographic	Highest level of education obtained	Ordinal
**Progression of MCI to dementia**	Clinical diagnosis	Use of neurocognitive screening (e.g., MoCA, clinical dementia rating) and final adjudication made through consensus management	Binary
**COVID-19 status**	*Previously confirmed COVID-19 history	COVID-19 positive or COVID-19 negative	Binary
**Sex**	Demographic	Male or female	Binary

Note. Neurovascular coupling (NVC), Functional near-infrared spectroscopy (fNIRS), Oxy-hemoglobin (HbO), Electroencephalography (EEG), Dynamic retinal vessel analysis (DVA), Laser speckle contrast imaging (LSCI), Flow mediated dilation (FMD), Hydroxyl radical antioxidant capacity assay (HORAC), White mattery hyperintensity (WMH), Montreal cognitive assessment (MoCA), Mild cognitive impairment (MCI), Adverse childhood experience (ACE).

* Indicates COVID-19 was confirmed by PCR or serologic testing.

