### 2.10 Data collection process

Patients who have consented to the study are interviewed for demographic information (sex, age, race education), COVID-19 history (symptoms during infection, and symptoms without confirmed infection), COVID-19 vaccine history, medical history (oncological, genitourinary, gastrointestinal, respiratory, endocrine, neurological, cardiovascular, musculoskeletal, and psychological conditions), screened for DVA (eye surgery history, photosensitive epilepsy, glaucoma, allergies to tropicamide), and social history (previously or current use of tobacco, alcohol, and recreational drugs, and adverse childhood experiences). Medication list is obtained from all patients, and common age-related conditions (i.e., hypertension, diabetes) must be pharmacologically controlled. All patients enrolled have baseline MRI data with neuroradiologic report at MCI diagnosis. Every 6 months patients have repeat neurocognitive screening and evaluation through OUHSC Department of Neurology faculty to identify if patients have progressed from MCI to dementia. Physiologic, circulating factors, and cognitive data is obtained from patients at visit one and at 18-month follow-up. Patients are scheduled through the Department of Neurology for a second MRI to obtain neuroradiologic report at 18-month follow-up after visit one.

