### 3.3 Circulating factors

Forty mL of blood will be taken from patients and centrifuged for 10 minutes at 1600 RPM or 15 minutes at 2500 RCF for separation of serum and plasma, respectively. Five, 500 μL samples of serum and plasma are aliquoted for each patient and samples are stored in a -80° freezer awaiting analysis of antioxidant capacity, cytokine levels, and endothelial biomarkers.

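### COVID-negative means only that no infection was confirmed, so unrecognised past infections sit among the controls and can attenuate the COVID+ v COVID- contrasts

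*Protocol article*

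**What the plan says.** The exposure definition appears in two places in the protocol article. Section 2.5 requires that patients with "a history of COVID-19 were confirmed by PCR or serology" and states no test for anyone else. Table 1 in section 2.9 lists COVID-19 status as binary, positive or negative, with the method of measurement given as "Previously confirmed COVID-19 history". Its footnote reads "Indicates COVID-19 was confirmed by PCR or serologic testing", which describes proof of infection and not proof of its absence.

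Section 2.1 describes the comparison group only as exposed patients "compared to MCI patients with no history of COVID-19 infection".

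Section 2.10 says that the interview covers "COVID-19 history (symptoms during infection, and symptoms without confirmed infection". The study therefore expects people with suspected but unproven infection and records them, but Table 1 has no category for them.

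After entry, section 2.2 follows status by PCR result and symptoms, given as examples. Section 2.4 anticipates that 5–15% of controls will become infected over the 18 months. It makes no allowance for infection before Visit 1 that went unrecognised.

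Section 3.3 says that "samples of serum and plasma are aliquoted for each patient". The assays listed in section 3.3 cover antioxidant capacity, cytokines and endothelial markers. None is a SARS-CoV-2 antibody test.

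**The concern.** A positive needs a PCR or serology result. A negative is what remains. When exposure is confirmed on one side only, the unexposed group holds two kinds of people: those never infected, and those infected without a confirming test.

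The COVID+ v COVID- label drives the cross-sectional comparison of NVC in section 4.1. It also drives the longitudinal comparisons in section 4.2, including the group interactions with NVC and WMH burden. If some controls were infected, and infection has the effect that the study hypothesises, the control group's progression, NVC and WMH move towards those of the COVID+ group. The estimated effect of COVID-19 is then too small, and a weak or null result is hard to interpret. The allowance in section 2.4 does not cover this, because it concerns infections that occur later.

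**Working it through.** **Inputs from section 2.4.** Progression was 10/18 = 55.6% in patients who contracted COVID-19 and 23/100 = 23% in those described as never infected. Total enrolment is up to 200, with dropout of at most 10%, so about 200 × 0.9 = 180 are evaluable.

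**The plan's own figure.** The stated p = 0.011 for 10/18 v 23/100 reproduces with the continuity-corrected chi-square (0.0108; Fisher's exact test gives 0.0087).

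**Assumptions, none given in the documents.** Let m be the share of labelled controls with an unrecognised past infection. Let f be the fraction of the excess risk that such an infection carries (1 = same as confirmed, 0.5 = half). Two splits of the 180 are used: 90 v 90, and 30 v 150, which is close to the 18:100 ratio of the earlier data. Tests are two-sided at 5%.

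**Formulas.**
- Observed control rate: c = 0.23 + m × f × (0.556 − 0.23)
- Difference: d = 0.556 − c
- Odds ratio: (0.556/0.444) ÷ (c/(1 − c))
- Power: Φ[(d − 1.96 × s0)/s1], where s0 is the pooled and s1 the unpooled standard error of the difference

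**No contamination.** c = 0.23, d = 32.6 points, OR = 1.252/0.299 = 4.2.

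**m = 20%, f = 1.** c = 0.23 + 0.20 × 0.326 = 0.295; d = 26.1 points; OR = 1.252/0.419 = 3.0.

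**m = 20%, f = 0.5.** c = 0.23 + 0.20 × 0.5 × 0.326 = 0.263; d = 29.3 points; OR = 1.252/0.356 = 3.5.

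**Power at m = 20%, f = 1, 30 v 150.** The pooled rate is (30 × 0.556 + 150 × 0.2952)/180 = 0.339, s0 = 0.0947 and s1 = 0.0981. Then (0.2608 − 1.96 × 0.0947)/0.0981 = 0.77, which gives power of 78%.

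Over a range of m with f = 1:

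| m | control rate | difference (points) | OR | power 30 v 150 | power 90 v 90 |
|---|---|---|---|---|---|
| 0 | 23.0% | 32.6 | 4.2 | 93.8% | 99.6% |
| 10% | 26.3% | 29.3 | 3.5 | 87.4% | 98.4% |
| 20% | 29.5% | 26.1 | 3.0 | 77.9% | 94.9% |
| 30% | 32.8% | 22.8 | 2.6 | 65.5% | 87.6% |
| 50% | 39.3% | 16.3 | 1.9 | 37.9% | 59.2% |

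The row for 20% at half effect is the same as the row for 10% at full effect, because only the product m × f enters the formula.

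**Continuous outcomes.** With f = 1, a mean difference shrinks by the factor (1 − m). For an assumed standardised difference of 0.5 with 90 per group, power goes from 91.8% to 81.4% at m = 15% and to 65.1% at m = 30%.

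**The case against.** The strongest reply is that the article nowhere says what happens to people with symptoms and no test. They might be excluded, tested or assigned by a rule in a fuller document, and silence in a journal article is not an error. That would be decisive if the exposure variable had been left open. It was not: section 2.5 and Table 1 fix it as confirmed history, in two categories. Under that rule an unconfirmed infection is negative. What stands is that this follows from the stated definition and is not a sentence in the plan.

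Several stronger readings are tempting, and the documents do not support them.

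- *The study is underpowered because of this.* At 90 v 90 with the plan's rates, 20% contamination still leaves 95% power. The marked loss appears with unequal groups, smaller effects or heavy contamination, all of which are assumed.
- *Power falls below what the earlier data imply.* The 23% comes from patients called never infected, and how that was ascertained is not shown. If it was by the same record-based rule, 23% already contains some unrecognised infections, and diluting it again counts them twice.
- *Every contrast and every aim is biased to the null.* The direction depends on unrecognised infections acting like confirmed ones, and on misclassification being unrelated to outcome. Analyses within infected patients, such as variant and time since infection, are not diluted in this way. Aims 3 and 4 also ask about NVC and WMH in relation to progression, which does not rest on the COVID label alone.
- *Serology-only cases have no start date.* Table 1 counts time since infection from COVID-19 diagnosis, so a serology diagnosis supplies one. Only the variant variable needs the month and year of infection.
- *Vaccination makes the serology unreliable.* The confirming assay is not described, so this cannot be judged. Vaccination history is collected and enters the analyses.

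**Conclusion.** The point holds in limited form. The stated definition places unconfirmed past infections in the control group, and the only allowance for infected controls concerns new infections during follow-up. If those earlier infections act in the same direction as confirmed ones, the COVID+ v COVID- contrasts in sections 4.1 and 4.2 are attenuated.

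At an assumed 20% contamination the risk difference loses between 3.3 points (32.6 − 29.3, half effect) and 6.5 points (32.6 − 26.1, full effect). The odds ratio falls from 4.2 to between 3.5 and 3.0. The contamination rate, the group split and the effect of unrecognised infection are all assumptions, so these figures show sensitivity and do not estimate what will happen.

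The main consequence is a biased effect estimate. Loss of power is secondary and depends on the split. This is a worthwhile and cheap improvement, not a flaw that undermines the design.

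**What to change.** 1. In section 2.5 and Table 1, define three classes: confirmed positive (PCR or serology), possible (symptoms without confirmed infection, from the section 2.10 interview) and negative.
2. In sections 4.1 and 4.2, repeat each primary COVID+ v COVID- contrast with the possible class left out of the controls, as a sensitivity analysis. Report the size of that class.
3. Leave cases whose infection date is unknown out of the variant analysis. The time-since-infection variable needs no change, since it runs from diagnosis.
4. Optionally, where stored Visit 1 serum allows, use an infection-specific antibody assay that vaccination does not trigger to reclassify controls. State that a negative result does not exclude past infection.

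Items 1 to 3 use data already collected. The price is a smaller control group in the sensitivity analysis and some loss of cases from the variant analysis. They deal only with symptomatic unconfirmed infection; infection without symptoms would remain among the controls. Item 4 addresses part of that remainder, but it is an added test and uses stored sample, so it should stay a choice for the investigators.

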### 2.6 Exclusion criteria

Vision or hearing impairment that would hinder the ability of participants to complete the study protocolChronic uncontrolled conditions (e.g., type 2 diabetes, hypercholesterolemia, hypertension)Current cerebrovascular complications or prior complications that are clinically deemed as exclusion to the study (i.e., large vessel stroke with chronic impairment)Neurodegenerative diseases (e.g., Parkinson’s, any types of dementia)Eye pathologies contraindicating dynamic retinal vessel analysis (DVA): Glaucoma, shallow anterior chamber (Van Herick Grade 2–0), intraocular pressure (IOP) >21mmHg, diabetic retinopathy, distinct cataract, photosensitive epilepsy, allergy to tropicamide.Medical conditions which, in the opinion of the investigative team, would render the patient inappropriate or too unstable to complete study protocol.

### 2.7 Primary outcome

The primary outcome of interest is whether COVID-19 contributes to the progression of MCI to dementia through impairment of NVC response, and promotion of white matter damage. Diagnosis of MCI and progression to dementia will be made clinically through the OUHSC Department of Neurology. Trained investigators will perform NVC measurements (fNIRS, electroencephalography [EEG], DVA) at baseline and 18 months follow-up. Burden of white matter damage (WMH) will be neuroradiologically assessed by the clinical neurology and neuroradiology team at baseline (at diagnosis of MCI prior to COVID-19 pandemic) and 18-month follow-up.

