#### 3.1.2 Neuroimaging investigations

Prior to visit one, patients were diagnosed with MCI and neuroradiologically (i.e., MRI) assessed for small vessel complications. In a recent meta-analysis from Guo and Shi, small vessel ischemic damage to the brain, evidenced by white matter hyperintensities (WMH) on MRI, was associated with increased risk of development of MCI and dementia [50]. Ischemia localized to, and originating from small vessels, and microbleeds are two common pathologies in cerebral small vessel disease (CSVD) [51], and can be imaged by MRI through T2 fluid attenuated inversion recovery (FLAIR) and T2* gradient echo (GRE) or susceptibility weighted imaging sequences (SWI), respectively. All study participants, in addition to the first MRI scan performed as a point of care before enrollment into the study, will be neuroradiologically evaluated at Visit 2 using a 3T MRI. Increased burden of WMH (i.e., confluence of deep foci and extension of periventricular WMH into the deep white matter) are one of the most common manifestations on T2 FLAIR MRI imaging for diagnosis of CSVD [52] and is associated with acute and recovered COVID-19 patients [22]. Moreover, burden of WMH, determined by Fazekas scale [53], will be longitudinally assessed as a contributing factor for conversion of MCI to dementia in COVID-19 patients. The Fazekas scale grades the periventricular and deep white matter from 0–3, depending on the size and confluence of the lesions [53,54]. This grading system is the most widely used system to date to identify severity of white matter pathology [53,55]. Additionally, presence of microbleeds will be neuroradiologically assessed, as this pathology is also associated with COVID-19 and has a specific pattern of distribution that distinguishes CSVD burden in recovered and acute COVID-19 patients from other known causes (i.e., hypertension, acute respiratory distress syndrome) [22].

WMH burden will be evaluated at baseline by Fazekas scale to determine if there are differences at diagnosis that could influence results at cross-sectional cognitive and physiological measurements. Longitudinally, WMH burden will be calculated at 18-months to determine the influence of WMH on progression to dementia and whether COVID-19 increases burden of WMH in patients with MCI.

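### The WMH baseline in 2.7 and Fig 1 (MRI at a pre-pandemic MCI diagnosis) is not what the entry criteria require, so WMH change may start after infection or span years instead of 18 months

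*Protocol article*

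**What the plan says.** Two sections of the protocol article define the WMH baseline as a pre-pandemic scan:

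- Section 2.7 (Primary outcome) sets the assessments "at baseline (at diagnosis of MCI prior to COVID-19 pandemic) and 18-month follow-up".
- The Fig 1 legend has "baseline MRI recorded at diagnosis of MCI prior to COVID-19 pandemic".

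The other sections carry no pandemic condition:

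- Section 2.5 requires an MCI diagnosis and the availability "of an MRI scan before study" enrolment, with no date limit.
- Section 2.10 states: "All patients enrolled have baseline MRI data with neuroradiologic report at MCI diagnosis".
- Section 3.1.2 refers to "the first MRI scan performed as a point of care before enrollment into the study".
- Section 2.2 says that, upon enrolment, "cognitive status and WMH status (MRI scan) will be recorded".

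Nothing in 2.5 or 2.6 requires the diagnosis or the scan to predate the pandemic or the infection. Section 2.6 excludes dementia. Sections 2.10 and 3.7 time the second MRI at 18 months after Visit 1, not after the first MRI. Section 4.2 puts change in WMH burden, and an interaction of WMH burden with COVID group, into the primary longitudinal analysis. Aim 4 asks whether COVID-19 raises WMH burden and whether that burden contributes to conversion.

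**The concern.** A change score needs a defined starting point. Here the outcome definition gives one and the entry criteria admit patients who cannot meet it. A patient who was infected, then diagnosed with MCI and scanned, then enrolled, is an eligible COVID+ case. Whatever WMH the infection had caused by the scan date already sits in that patient's baseline.

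The pre-pandemic reading avoids this but brings two other consequences. The change is measured over several years, not over the 18 months of follow-up. And because dementia is an exclusion, only patients who stayed dementia-free from diagnosis to entry can be enrolled.

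WMH change is one of the two mechanisms in the primary outcome, so it matters which reading applies.

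**Working it through.** The protocol gives no figure to reproduce on this point. The check sets the definitions side by side and then does calendar arithmetic on the protocol's own timeline.

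**1. Are the definitions compatible?** They are nested. A scan at a pre-pandemic diagnosis also satisfies 2.5, 2.10 and 3.1.2. The reverse fails: a patient diagnosed and scanned after the pandemic began satisfies those three sections and cannot have the baseline of 2.7 and Fig 1.

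**2. Interval if all index scans are pre-pandemic.**

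Inputs from 3.7: enrolment lasts 2 years, the second MRI is 18 months after the baseline visit, and follow-up ends in 2026. Assumptions: the pandemic began between December 2019 and March 2020, and follow-up ends between January and December 2026.

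Last Visit 2 = end of follow-up. First Visit 2 = end minus 24 months. Visit 1 = Visit 2 minus 18 months. The latest possible pre-pandemic scan is at onset, so these are minimum intervals:

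| Assumed onset | Assumed end | Scan to first Visit 2 | Scan to last Visit 2 | Scan to Visit 1 (first; last patient) |
|---|---|---|---|---|
| Mar 2020 | Jan 2026 | 46 months | 70 months | 28; 52 months |
| Dec 2019 | Jan 2026 | 49 months | 73 months | 31; 55 months |
| Mar 2020 | Dec 2026 | 57 months | 81 months | 39; 63 months |
| Dec 2019 | Dec 2026 | 60 months | 84 months | 42; 66 months |

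The minimum interval is therefore 46 to 84 months (3.8 to 7.0 years). A scan made just before enrolment gives about 18 months. The ratio is 46/18 = 2.6 to 84/18 = 4.7. Even with only pre-pandemic scans, two-year enrolment adds up to 24 months of spread.

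**3. What an unequal interval could do.** Suppose, for illustration only, that Fazekas grade rises at a constant rate g per year with no COVID-19 effect. Expected change is g × months/12:

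| Assumed g (grade/year) | 18 months | 46 months | 84 months |
|---|---|---|---|
| 0.05 | 0.075 | 0.19 | 0.35 |
| 0.1 | 0.15 | 0.38 | 0.70 |
| 0.2 | 0.30 | 0.77 | 1.40 |

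The spurious group difference is g × (difference in mean interval, in years). At g = 0.1, if one group had only 18-month intervals and the other only 46- or 84-month intervals, it would be 0.1 × 28/12 = 0.23 or 0.1 × 66/12 = 0.55 grade. These are extremes. If the groups have the same mean interval, the difference is zero.

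**4. What a post-infection index scan does.** Let d be the WMH increase caused by infection, p the share of COVID+ patients whose index scan follows infection, and f the share of d already present at that scan. With additive effects and equal intervals, the group difference in change estimates d × (1 − p × f). This equals d when p = 0 and falls towards zero as p and f approach 1. The documents give neither p nor f.

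**5. Do the listed variables resolve it?** Table 1 measures time since infection from COVID-19 diagnosis to Visit 1. It does not order scan and infection, and it has no value for controls. Section 3.1.2 compares baseline Fazekas grades between groups, which also does not establish the order.

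**The case against.** The strongest reply is that 2.5 states a minimum condition while 2.7 and Fig 1 define the baseline, and 2.10 ties the scan to MCI diagnosis. On that view no contradiction arises, and interval covariates belong in a statistical analysis plan that is not shown. Part of this stands: the definitions are nested, and the absence of a covariate from a condensed article would not be a finding in itself. But an analysis plan cannot decide who is eligible or which scan is the baseline, and on those the article's sections disagree.

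Three stronger readings are tempting, and the documents do not support them.

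- *Baselines are in fact mixed, and all the harms apply together.* The criteria permit mixing; nothing shows how often it happens. For any one patient the harms are alternatives: a pre-pandemic scan cannot follow infection, and entry is not confined to long-term dementia-free patients if recent diagnoses are admitted.
- *The dementia exclusion has removed a known and large share of patients, and more of the infected.* The annual conversion rates cited in the Introduction run from 3–4.9% in community settings to 23.8% in disadvantaged areas. The progression data in 2.4 come from a cited study, with no follow-up time given for the two rates and no statement that those patients form the recruitment pool. Assuming greater loss among the infected presumes the hypothesis under test.
- *The primary analysis is biased towards no effect.* That direction holds for WMH change as an outcome. In 4.2 WMH change is a predictor of progression with a group interaction, and no direction has been derived for that model.

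**Conclusion.** The concern holds in a limited form. Section 2.7 and Fig 1 fix a baseline that 2.5, 2.10 and 3.1.2 do not require, and the primary longitudinal analysis uses the change from it. If post-infection scans are admitted, the COVID-19 effect on WMH change is understated by an amount the documents do not allow one to size. If all scans are pre-pandemic, the change covers at least about 4 to 7 years, and entry is conditional on at least 28 to 66 months without dementia since diagnosis. These spans rest on the assumed pandemic onset and on the assumed month in which follow-up ends in 2026. Interval differences confound the COVID-19 contrast only if they are related to group, which is not shown. The definition needs correcting before WMH change is analysed.

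**What to change.** 1. State one index-MRI rule in 2.5, 2.7, 3.1.2 and Fig 1, and align 2.10. If a pre-pandemic diagnosis is not an entry rule, delete that qualifier from 2.7 and Fig 1.
2. Record the dates of MCI diagnosis, index MRI and, where known, first infection.
3. Include the scan-to-scan interval in every WMH-change model, for both groups.
4. Base the Aim 4 effect of COVID-19 on WMH change on COVID+ patients whose index MRI predates infection. Compare them with controls over comparable scan intervals, with interval adjustment, and report all patients as a sensitivity analysis. Restricting only the COVID+ group, with no condition on controls, would tend to give that group older scans and create the imbalance to be avoided.
5. Add time from MCI diagnosis to Visit 1 as a covariate in the logistic progression models.

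The cost is a short amendment and the collection of three dates. Fewer COVID+ patients will contribute to the main WMH-change analysis, though they remain in the others. Section 2.5 accepts serology as confirmation, so some infections may not be datable, and those patients could enter only the sensitivity analysis.
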